#### Randomization procedure

2.5.2

The MOVE12-pilot study was designed as a two-arm, three-level cluster randomized controlled trial (RCT), featuring an intervention group (IG) and a control group (CG), with participants organized within classrooms and schools. Participants were randomly assigned to either the IG or the CG (1:1) by the principal investigator (PI). At the three academic schools (class size: 25–30), four relatively homogeneous classes were identified, and randomization involved drawing from two boxes (one for group assignment, one for classes) in alternating turns until all classes were assigned. At the two vocational schools (class size: 12–17), classes were stratified by gender, size, and subject area before following the same procedure using four boxes (A–D). Twice as many groups were drawn from the vocational school that was double the size of the others.

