### Quantitative and qualitative data analysis

2.7

Data analysis will combine quantitative and qualitative approaches. To examine between-group differences in continuous outcome measures from baseline to the 12-week follow-up, a linear mixed model (LMM) will be applied. LMM addresses the nested data structure of MOVE12 (students within classrooms, classrooms within schools) by incorporating random intercepts to account for intra-class correlation and hierarchical clustering effects (71). Additionally, LMMs handle missing data robustly under the assumption of missing at random (72), a common scenario in school-based interventions. Within-group changes will be assessed using dependent *t*-tests, and potential associations between ordinal outcome measures will be explored through multiple and binary regression analyses. All statistical analyses will be conducted using STATA version 18.0 (73).

Qualitative methods will be used to identify key themes from the planned focus group interviews, guided by determinants such as knowledge, attitude, self-efficacy, basic psychological needs (autonomy, competence, relatedness), social support, school culture, and the physical environment. This qualitative approach aims to deepen our understanding of how these factors influence participants' experiences and engagement with the intervention, thereby informing both practical implementation and theoretical implications. Qualitative data will be analyzed thematically using NVivo 14 software to support and manage the analytic process (74).

*a priori* sample size calculations with G-Power (75) suggested that a sample of 580 participants would be sufficient to detect a moderate effect size (*d* = 0.3), assuming a two-group design, 80% power, and an alpha of.05.

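### The stated random intercepts do not ensure that class-level variation in change reaches the treatment-effect standard error, because the form of the mixed model is left open

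*Protocol article*

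**What the plan says.** In the protocol article, under Quantitative and qualitative data analysis, the comparison of arms is described as follows: "To examine between-group differences in continuous outcome measures from baseline to the 12-week follow-up, a linear mixed model (LMM) will be applied". The nesting to be handled is "students within classrooms, classrooms within schools", and the device is the model's random intercepts: "by incorporating random intercepts to account for intra-class correlation and hierarchical clustering effects". The same paragraph gives as a further advantage that "LMMs handle missing data robustly under the assumption of missing at random".

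The section does not say whether the baseline value is an outcome or a covariate. It names no group-by-time term, no student-level random effect for repeated measures, and no random effect that lets a class change over time.

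Under Randomization procedure, whole classes are drawn to the arms within each school, "in alternating turns until all classes were assigned". In the vocational schools, "classes were stratified by gender, size, and subject area" before the draw. Under Secondary outcome measures, most continuous outcomes are measured twice, at baseline and at 12 weeks.

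**The concern.** In a class-randomised trial, the treatment-effect standard error must contain the variation between classes in whatever quantity the arms are compared on. Here that quantity is a difference over time. A random intercept for class describes how far a class lies above or below average at every occasion. It says nothing about how much the class changes.

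The document itself gives grounds to expect classes to differ in change. Student pairs lead the breaks for their own class, teachers coordinate the rotation, and the Discussion expects uneven resources and commitment to affect how consistently the intervention is delivered. One outcome, the learning environment, is close to a property of the class.

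If that variation is left in the residual as though students were independent, intervals are too narrow and chance differences are declared significant too often. A larger main intervention is planned after this pilot, so false signals on activity, fitness or wellbeing could mislead it.

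**Working it through.** The plan gives no figure on this point to reproduce. The check asks what the stated device does under each model that the text permits.

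**Inputs from the document.** Classes are randomised within schools; class sizes are 25–30 (academic) and 12–17 (vocational); 519 of 739 eligible students consented; there are two occasions.

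**Assumptions.** The document gives no ICC for change (ρ), no baseline–follow-up correlation (r) and no number of vocational classes. Analysed class size m is taken as 12 to 27 and ρ as 0 to 0.10.

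**Step 1: two records per student, intercepts for class and student.** Write y(t) = fixed part + class + student + error(t). Then y(12 weeks) − y(baseline) contains neither the class nor the student intercept, and a school intercept drops out in the same way. With complete data, the group-by-time estimate is the plain difference in mean changes, and its model standard error has no class term. A direct fit to one simulated data set (8 classes of 8) confirmed this:

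| Analysis | Estimate | SE |
|---|---|---|
| Mixed model, class and student intercepts | −0.0506 | 0.2315 |
| Difference in changes, ignoring class | −0.0506 | 0.2316 |

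**Step 2: size of the error.** The true variance is larger by DE = 1 + (m − 1)ρ, and type I error = 2[1 − Φ(1.96/√DE)].

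| ρ | m = 12: DE, type I | m = 27: DE, type I |
|---|---|---|
| 0 | 1.00, 5.0% | 1.00, 5.0% |
| 0.01 | 1.11, 6.3% | 1.26, 8.1% |
| 0.02 | 1.22, 7.6% | 1.52, 11.2% |
| 0.05 | 1.55, 11.5% | 2.30, 19.6% |
| 0.10 | 2.10, 17.6% | 3.60, 30.2% |

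For example, with m = 27 and ρ = 0.05: √2.30 = 1.517, 1.96/1.517 = 1.292, two-sided tail 19.6%.

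If consent (519/739 = 70%) were even across classes, m would run from about 8 (12 × 0.70) to 21 (30 × 0.70). At ρ = 0.05, DE is then 1.35 to 2.00 and type I error 9.2% to 16.6%. The figures are somewhat lower but the conclusion is the same.

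**Step 3: simulation.** With 34 classes, 504 students and 150 runs per setting (Monte Carlo error about 2 to 3 percentage points):

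| ρ | Two occasions, intercepts only | 12-week value on baseline, class intercept |
|---|---|---|
| 0 | 4.7% | 2.7% |
| 0.025 | 8.7% | 4.0% |
| 0.05 | 14.0% | 4.0% |
| 0.10 | 21.3% | 4.7% |

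**Step 4: two records per student, no student intercept.** The levels listed are student, class and school, with no level for occasion within student. Fitted literally to two occasions, the model treats a student's two values as independent given class. Ignoring class variation in change, model SE/true SE = √[1/(1 − r)], which is 1.41 at r = 0.5 and 2.24 at r = 0.8. In the data set of Step 1 the SE was 0.315 instead of 0.231. Class variation in change pulls the other way, so the ratio becomes √{1/[(1 − r)DE]}. At r = 0.5 and DE = 2.30 it is 0.93, so the overstatement is usual but not universal.

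**Step 5: one record per student.** If the outcome is the 12-week value adjusted for baseline, or the change score, the class intercept is the class variation in the quantity compared. It enters the standard error, as the last column of Step 3 shows.

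**The case against.** The strongest reply is that the criticised model is inferred. The text never says that intercepts are the only random effects and names no group-by-time term. Student, class and school are the complete set of levels for one record per student, and the Randomization procedure section likewise calls the design three-level. On that reading the class intercept works, and the remedy proposed here may be what is already intended. The missing-data sentence states a general property of mixed models and does not settle the form. This stands as far as it goes: the document permits a valid model. It does not remove the point, because offering missing-at-random handling as an advantage, with two occasions, points more naturally to both being outcomes, and there the stated device fails.

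A reader might go further and infer that the intervals of every continuous outcome are wrong whichever model is fitted. The document does not support that. The one-record model is sound; at zero class variance in change the two-occasion model with a student intercept is also correct; and heart rate and the attention tests are tied to a mid-intervention session, so this contrast does not apply to them.

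Nor does silence on the randomisation strata show that they are omitted from the model. No fixed effects are listed at all, and an article may leave these to the analysis plan.

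**Conclusion.** The point holds as a should-fix. A single sentence claims that clustering is handled while permitting a model with valid inference, one with inflated type I error and one whose standard errors tend to be too large. On the more natural two-occasion reading, random intercepts alone leave class-level change out of the treatment-effect standard error.

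With a student intercept, type I error is about 8–11% at ρ = 0.02 and 12–20% at ρ = 0.05, for 12–27 analysed students per class. These sizes rest on assumed ICCs and class sizes and are not predictions for this trial. That type I error exceeds 5% whenever classes differ in change is a property of the model and does not depend on those values.

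The reach is limited to secondary continuous outcomes measured at baseline and 12 weeks. The primary outcomes concern adherence and experience, assessed through focus groups, and are not touched.

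**What to change.** State the model explicitly. The preferred form is the 12-week value regressed on arm and baseline value, with school as a fixed effect (and the vocational randomisation stratum where the number of classes allows) and a random intercept for class. Fit it by REML with a small-sample degrees-of-freedom correction such as Kenward–Roger, which the planned software offers for mixed models.

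If both occasions are to stay in the outcome, include a student random intercept and a class-by-time random effect, with the same small-sample correction.

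The cost is about two sentences and a change to the analysis code. Intervals will be slightly wider where classes differ in change, and the fixed effects use a few degrees of freedom. The one-record form drops students without a 12-week value, whereas the two-occasion form keeps them. That trade-off should decide between the two, and the missing-data sentence should be worded to match the choice.

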**Results:**

Linear mixed models, *t*-tests, and regression analyses will evaluate quantitative outcomes, while qualitative focus groups will explore engagement and behavior change.

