### Program implementation plan

2.5

The fifth step of the IM protocol process focused on planning the adoption, implementation, and sustainability of the intervention. This stage emphasizes engaging stakeholders to address barriers and refine strategies to maximize the intervention's reach and impact. Stakeholder discussions played a pivotal role in shaping the implementation plan. For example, feedback from school leaders and teacher ambassadors highlighted the need for financial incentives to encourage teacher ambassadors' active involvement. This input led to the allocation of dedicated funding to support their roles, ensuring consistent oversight and motivation during the intervention. Additionally, the needs assessment highlighted the importance of tailored communication strategies for parents to foster engagement and extend the program's impact beyond the classroom. In response, an information letter was developed to emphasize the benefits of MOVE-breaks in enhancing students' physical activity levels and overall well-being. As illustrated in Figure 3, the implementation of MOVE-breaks commenced following the completion of baseline measurements at the end of January 2023 and continued for a 12-week period, concluding in April 2023. This timeline allowed for a structured rollout while maintaining flexibility to address any unforeseen challenges. By incorporating the iterative refinements, the implementation plan was aligned with the practical needs of schools and stakeholders, enhancing the likelihood of sustained adoption and success.

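### The dependent t-tests of within-group change ignore class clustering and any change common to both arms; report within-arm change descriptively from a suitably clustered model instead

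*Protocol article*

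**What the plan says.** Section 2.7 (Quantitative and qualitative data analysis) sets out two analyses of change in continuous outcomes.

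- Between arms: "To examine between-group differences in continuous outcome measures from baseline to the 12-week follow-up, a linear mixed model (LMM) will be applied". The model deals with nesting "by incorporating random intercepts to account for intra-class correlation and hierarchical clustering effects", and a second reason given for it is that "LMMs handle missing data robustly under the assumption of missing at random".
- Within arms: "Within-group changes will be assessed using dependent" *t*-tests. No cluster adjustment, descriptive label or rule of interpretation is attached.

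The Results paragraph of the abstract ranks neither above the other: "Linear mixed models, *t*-tests, and regression analyses will evaluate quantitative outcomes". Section 2.5.2 (Randomization procedure) describes drawing whole classes to the arms. Section 2.5 (Program implementation plan) starts the intervention after "the completion of baseline measurements at the end of January 2023" and ends it in April 2023. Section 2.6.2 lists the quantitative outcomes as secondary. Most of them, including accelerometer activity, fitness tests and questionnaires, are taken at baseline and 12 weeks.

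**The concern.** Both reasons given for the LMM, nesting and missing data, are lost in the dependent *t*-tests. A paired test has no class term and drops every student without both measurements.

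There are two separate consequences. First, if classes differ in how much their students change, the standard error is too small and the test rejects too often, even for its own hypothesis of no change. Second, each test uses one arm only, so season, maturation and familiarity with the tests enter the estimate in full. A significant change in the intervention arm beside a non-significant one in the control arm is not evidence of a difference between arms, but reporting the two tests side by side invites that reading. A larger main intervention is planned after this pilot, so a false signal could carry forward.

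**Working it through.** The article gives no figure for the behaviour of these tests, so there is none to reproduce.

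**Inputs from the article.** 519 students consented, about 260 per arm at 1:1. Three academic schools supplied four classes each, 12 in all. The two vocational schools contributed about 200 + 100 = 300 students in classes of 12–17, which is 300/17 ≈ 18 to 300/12 = 25 classes; 20 is taken here. That makes about 32 classes, or 16 per arm, and 519/32 ≈ 16 consenting students per class.

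**Assumptions, not in the article.** The share of the variance of change that lies between classes (change-score ICC) is 2%, 5% or 10%. The drift common to both arms is 0.1 or 0.2 SD of the outcome. The correlation between baseline and follow-up is 0.5 to 0.7.

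**1. Clustering, with no true change.** Stable class differences cancel in a paired difference; only class-to-class variation in change matters. With m students per class the true variance of the mean change is larger than the *t*-test assumes by DE = 1 + (m − 1) × ICC, and the actual type I error is 2 × [1 − Φ(1.96/√DE)]. With m = 16:

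| ICC of change | DE | 1.96/√DE | Type I error, formula | Type I error, simulation |
|---|---|---|---|---|
| 2% | 1.30 | 1.72 | 8.6% | 8.5% |
| 5% | 1.75 | 1.48 | 13.8% | 13.4% |
| 10% | 2.50 | 1.24 | 21.5% | 22.4% |

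The simulation used 20,000 trials with 16 classes of 16 per arm. A one-sample *t*-test on the 16 class-mean changes held 4.7–5.2% in the same data.

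**2. Common drift, with no intervention effect and no clustering.** The standardised change is dz = d/√(2(1 − r)). The probability p that one arm is significant comes from the noncentral *t* distribution with n = 260. The arms are independent, so the intervention arm alone is significant with probability p(1 − p).

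| Drift d | r | dz | p, one arm | Intervention only, p(1 − p) |
|---|---|---|---|---|
| 0.1 | 0.5 | 0.100 | 36.2% | 23.1% |
| 0.1 | 0.7 | 0.129 | 54.5% | 24.8% |
| 0.2 | 0.5 | 0.200 | 89.5% | 9.4% |
| 0.2 | 0.7 | 0.258 | 98.6% | 1.4% |

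A valid two-sided 5% comparison of the arms would favour the intervention in 2.5% of such trials. At the larger drift the misleading pattern becomes rarer because both arms are usually significant.

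**3. Would the planned LMM give a sound within-arm contrast?** Suppose it is fitted to the repeated measures with random intercepts only. In balanced, complete data its within-arm time contrast is then essentially the paired *t*-test with a variance pooled over arms. In the same simulated data that contrast rejected in 8.7%, 13.4% and 22.4% of trials at ICC 2%, 5% and 10%. Random intercepts alone therefore do not repair the within-arm test.

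**The case against.** The best defence is that the plan already makes the randomised comparison. The same paragraph assigns it to an LMM that models class and school, and the *t*-tests are a separate statement about change over time. That stands: a reader might infer that the trial gives up its between-arm comparison, but this is true of the *t*-tests only.

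A reader might also infer that the tests are bound to show improvements that MOVE-breaks did not cause. The article does not support that. It gives neither the size nor the direction of any drift, and a drift towards worse values would show no improvement. A test that detects real change over time is also not wrong about its own hypothesis; the error lies in reading it as an effect, and no section says it will be read so. Nor does any section exclude it, and the abstract sets *t*-tests beside the LMM without distinction.

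The consequence is limited too. This is a pilot whose primary outcomes are adherence and experience, so only secondary outcomes are touched. The Flanker and Stroop tests, taken before and after one mid-intervention session, fall outside the baseline-to-12-week LMM as described. A reader might infer that a dependent *t*-test is their only analysis, but the article does not say so.

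None of this answers the clustering point. That needs no misreading: the p-values are too small for the hypothesis they test whenever change varies between classes.

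**Conclusion.** The point holds in a limited form. The article prespecifies a test that ignores the unit of randomisation, immediately after giving nesting and missing data as reasons for a different model. This is a stated analysis with understated standard errors, not an omitted detail. The inflation, to about 8.5%, 14% and 21% against a nominal 5%, rests on assumed change-score ICCs of 2%, 5% and 10% and on roughly 16 classes of 16 per arm. Any positive ICC inflates the error. The drift result, 23–25% at 0.1 SD and 1–9% at 0.2 SD, rests on assumed drift and correlation, and does harm only if within-arm significance is taken as an effect. The planned between-arm analysis is not displaced. The change should be made, but it does not threaten the trial's primary aim.

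**What to change.** 1. Delete the dependent *t*-tests from section 2.7, and amend the abstract to match.
2. Report each arm's change from baseline to 12 weeks with a 95% confidence interval, descriptively and without a p-value. Take it from the LMM extended by a class-by-time random effect, or use class-level cluster-robust standard errors.
3. State that conclusions about the effect of MOVE-breaks rest only on the between-arm contrast.

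The cost is small but not nil: one more variance component to estimate, and wider within-arm intervals. Relative to the paired *t*-test, the standard error grows by √DE, which is 1.14, 1.32 and 1.58 at the three assumed ICCs. At the low end the change is slight, and at any ICC the extra width is the uncertainty that the *t*-test leaves out. No new data are needed.

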#### Secondary outcome measures

2.6.2

Additionally, the study aims to evaluate potential effects of MOVE-breaks on physical fitness, psychosocial health parameters, and school-related factors through the following outcome measures:
-Attention and Concentration: Measured with the Eriksen Flanker Test (56) and the Stroop Test (57) before and after a designated MOVE-break session at the midpoint of the intervention.-Heart Rate Measurements: Measured during a designated MOVE-break session at the midpoint of the intervention using the Polar Team Pro System (58).-Physical Activity Level: Measured using the ActiGraph wGT3X-BT (59) at baseline and 12-week follow-up.-Aerobic Fitness: Measured with the YMCA 3-min step test (60) at baseline and 12-week follow-up.-Muscle Strength: Measured by (i) standing long jump (61) and ii) handgrip (dynamometer) (62) at baseline and 12-week follow-up.-Postural Balance: Measured by two-leg standing, eyes closed (30 s) and one-leg standing, eyes open (30 s) (63) at baseline and 12-week follow-up.-Flexibility: Measured by the sit-and-reach test (64) at baseline and 12-week follow-up.-Sleep Quality: Measured by an online questionnaire (Nettskjema.no) at baseline and 12-week follow-up using four single items from a modified version of the Karolinska Sleep Questionnaire (65).-Wellbeing: Measured by an online questionnaire (Nettskjema.no) at baseline and 12-week follow-up using the Warwick-Edinburgh Mental Wellbeing 7-item scale (66).-Self-Efficacy: Measured by an online questionnaire (Nettskjema.no) at baseline and 12-week follow-up using a factor developed by Sørlie and Nordahl (67), based on Bandura (68).-Learning Environment and Social Wellbeing in Class: Measured by an online questionnaire (Nettskjema.no) at baseline and 12-week follow-up using 13 items developed by Moos and Trickett (69), translated and processed by Sørlie and Nordahl (67).-Social Isolation: Measured by an online questionnaire (Nettskjema.no) at baseline and 12-week follow-up using 21 items from the Social Skills Rating System by Gresham and Elliott (70), translated and processed by Sørlie and Nordahl (67).

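### No comparison between arms is planned for outcomes treated as ordinal, and the regressions named for them do not suit ordered responses

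*Protocol article*

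**What the plan says.** Section 2.7 of the protocol article assigns methods by type of outcome.

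- **Continuous outcomes:** "To examine between-group differences in continuous outcome measures from baseline to the 12-week follow-up, a linear mixed model (LMM) will be applied". This model deals with the nesting of students in classes and schools "by incorporating random intercepts to account for intra-class correlation and hierarchical clustering effects".
- **Within-group changes:** dependent *t*-tests.
- **Ordinal outcomes:** "potential associations between ordinal outcome measures will be explored through multiple and binary regression analyses".

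No other quantitative analysis is described. Section 2.6.2 gives the purpose of the secondary outcomes: "the study aims to evaluate potential effects of MOVE-breaks on physical fitness, psychosocial health parameters, and school-related factors". Among them is sleep quality, measured "using four single items from a modified version of the Karolinska Sleep Questionnaire" at baseline and 12 weeks. Other psychosocial outcomes are multi-item instruments, for example wellbeing "using the Warwick-Edinburgh Mental Wellbeing 7-item scale". The article does not say which outcomes it regards as ordinal.

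**The concern.** The trial randomises classes in order to estimate what MOVE-breaks do. For an outcome classed as ordinal, the stated analysis answers another question, namely how outcomes relate to one another. The within-group *t*-tests do not fill the gap, because a change within one arm is not a comparison with the other. Followed as written, the plan would leave the effect on such an outcome unestimated.

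Two further matters follow from the methods named. Multiple regression, taken as linear, treats the response categories as equally spaced. Binary regression applied to an ordered response needs a cut point, which discards information, and an unstated cut point can be chosen after the data are seen. Random intercepts are described for the linear mixed model alone, so it is not clear what would protect these regressions if allocation, which is constant within a class, were a predictor.

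**Working it through.** The plan gives no figure on this point, so there is nothing to reproduce. The check has three steps.

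**1. Aim against analysis.**

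| | Continuous outcomes | Ordinal outcomes |
|---|---|---|
| Aim (2.6.2) | effect of MOVE-breaks | effect of MOVE-breaks |
| Between-arm model (2.7) | linear mixed model | none stated |
| Other analysis tied to outcome type (2.7) | none stated | associations between outcomes |
| Class and school effects (2.7) | random intercepts | not mentioned |

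The set of ordinal outcomes is not empty, since section 2.7 itself refers to ordinal outcome measures. Of the twelve secondary outcomes listed, sleep quality is the clearest candidate: it consists of single items and no summed score is described.

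**2. Cost of dichotomising, if that is done.** Under proportional odds, information is proportional to 1 − Σp³, where p are the category proportions. The number and frequency of response categories are not in the article and are assumed here.

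Five equal categories:
- all five kept: 1 − 5 × 0.2³ = 0.96
- 40/60 cut: 1 − 0.4³ − 0.6³ = 0.72, and 0.72 / 0.96 = 0.75
- 20/80 cut: 1 − 0.2³ − 0.8³ = 0.48, and 0.48 / 0.96 = 0.50

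Five equal categories cannot be split 50/50, so 0.75 is the best attainable. To recover the lost information, the sample would have to grow by 1 / 0.75 = 1.33 to 1 / 0.50 = 2.0 times. Other equal-category shapes give:
- four categories: 0.80 (middle cut) to 0.60 (end cut)
- seven categories: 0.75 (cut nearest the middle) to 0.375 (end cut)

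**3. Cost of leaving out class, if arm is tested that way.** Class sizes are from section 2.5.2: 12 to 17 in vocational schools and 25 to 30 in academic schools. The ICC is not given; 0.01 to 0.10 is assumed. The design effect is 1 + (m − 1) × ICC, the standard error is understated by its square root, and the true two-sided level of a nominal 0.05 test is 2 × [1 − Φ(1.96 / √DE)].

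| m | ICC | Design effect | SE factor | True level |
|---|---|---|---|---|
| 12 | 0.01 | 1 + 11 × 0.01 = 1.11 | 1.05 | 0.06 |
| 12 | 0.10 | 1 + 11 × 0.10 = 2.10 | 1.45 | 0.18 |
| 30 | 0.01 | 1 + 29 × 0.01 = 1.29 | 1.14 | 0.08 |
| 30 | 0.10 | 1 + 29 × 0.10 = 3.90 | 1.97 | 0.32 |

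These figures hold only for a predictor that is constant within a class, such as arm. An association between two student-level outcomes does not carry the full design effect. They also take every student in a class as analysed. Section 2.5.1 reports consent from 519 of 739 (519 / 739 = 70%), so the clusters analysed may be smaller and the upper end of the range is generous.

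**The case against.** The strongest defence is that the text supports less than a reader might infer from it, in four respects.

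- **Clustering.** A reader might infer that the ordinal regressions ignore class. The article does not say so. It recognises the nesting and is simply silent on variance estimation for exploratory models, which a condensed article may leave to a fuller document. This stands, so step 3 of the working is conditional.
- **Dichotomising.** A reader might infer that ordered items will be cut in two. No cut point or coding is given, and the binary regressions may be meant for variables that are binary to begin with. This also stands, so step 2 is conditional.
- **Reach.** A reader might infer that psychosocial effects in general go unestimated. The wellbeing, self-efficacy, learning-environment and social-isolation instruments may be scored as continuous and fall under the linear mixed model. The gap may be confined to one of twelve secondary outcomes, and the response format of the sleep items is not given. This stands too.
- **Model preference.** Linear analysis of Likert-type items is common, and an ordered logistic model brings its own proportional-odds assumption. That is fair, and it is why scoring the item as continuous in the linear mixed model is an acceptable answer, provided it is stated.

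It could also be said that the sentence was meant to cover associations between arm and ordinal outcomes. The words do not say that. If it was meant, the fit of the named regressions and the need for a class term would matter more.

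None of this supplies a between-arm analysis for ordinal outcomes. Nor is this a matter left to another document: the article names a question and a method for these outcomes, and neither serves the aim in section 2.6.2.

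**Conclusion.** The point holds in a limited form. As written, section 2.7 provides no estimate of the effect of MOVE-breaks on any outcome treated as ordinal, although section 2.6.2 asks for one, and the regressions it names are poorly suited to ordered responses.

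The mismatch between aim and analysis rests on the text alone. The sizes rest on assumptions: 25% to 50% of the information lost if a five-category item with equal frequencies is dichotomised, and a design effect of 1.11 to 3.9 left out if arm is tested without a class term at an ICC of 0.01 to 0.10. The documents do not show that either will happen.

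The severity is minor. The regressions are exploratory, the outcomes are secondary, and the primary outcomes of this pilot (section 2.6.1) concern participation and feasibility.

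**What to change.** 1. State in section 2.7 which outcomes are treated as ordinal.
2. For each, compare the arms at 12 weeks with a mixed-effects ordered logistic model (Stata `meologit`), with arm, baseline response and randomisation stratum as fixed effects and a random intercept for class. Report the between-arm odds ratio and check proportional odds. Alternatively, state that the item is scored as continuous and analysed in the linear mixed model.
3. Give any exploratory model of associations between outcomes the same class term. If a response is to be dichotomised, state the cut point in advance.

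The cost is a few sentences, one standard command in the software already named, and the check of proportional odds. No further data are needed.
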